The target population for the demonstration project will be heterosexual serodiscordant couples. Several studies have identified this as a priority population for this kind of intervention, but more than that, enough work has been done with this population in enough places that we now have sociological tools specific to them that we can use with some confidence. WHO, for example, is about to release guidelines for counseling serodiscordant couples about prevention; they will include ART and PrEP as prevention strategies. The study "Partner's PrEP," for another example, developed a simple and effective risk assessment tool that proved to be a good predictor of behaviors in this population. We intend to use it in this project to place participants.

The treatment strategy that will be used in this project adopt both TasP and PrEP. For a serodiscordant couple, PrEP and TasP work together for long-term prevention of HIV infection. ART, necessary for TasP, is not indicated for the infected partner until quite some time after initial diagnosis. Throughout this period, the uninfected partner is at elevated risk. However, if PrEP is adopted by the uninfected partner when the infected partner is diagnosed, that risk is significantly reduced. Eventually the infected partner begins ART

and sometime later achieves viral suppression. At this point as TasP strategy can be adopted and PrEP ended.

To start, a sample with a size of 600 heterosexual HIV-1 serodiscordant couples will be recruited for the study. PrEP would be administered through three sites selected from three States in Nigeria – Anambra, Cross River and Jos.

The project will have three primary goals:

- Construct a model that effectively delivers PrEP to serodiscordant couples. Within the context of this goal, the measure of effectiveness will be the number of new infections averted.
- Measure the cost effectiveness of the model. The measure of cost effectiveness will be cost per life-year gained and cost per infection averted
- Estimate what would be needed to scale up the delivery model to the national level.

Given the data and experience gained from the project, it should be possible to deliver a practical plan, complete with a budget estimate, to scale up PrEP and TasP, and make them part of a comprehensive national HIV prevention package.

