### 1.1 ART and HIV-I transmission

ART reduces HIV-1 transmission by reducing HIV-1 plasma concentrations to undetectable levels within 6 months of initiation in the majority of persons and seminal and cervicovaginal HIV-1 concentrations are also reduced to undetectable levels in most persons on ART. Also, the use of peripartum ART is responsible for the remarkable success in virtually eliminating mother-to-child HIV-1 transmission in resource-rich settings. The efficacy of antiretrovirals for the prevention of mother-to-child transmission of HIV-1, first demonstrated with peripartum zidovudine showed the feasibility of preventing sexual acquisition of HIV-1 with PrEP. More recent studies have shown that

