future ART costs among HIV-1-uninfected partners who remain uninfected. Second, PrEP in serodiscordant couples could be as cost-effective as earlier initiation of ART (compared to existing practice) if PrEP has a sufficiently high effectiveness (>70%) and low cost of delivery. If used in couples that remain at high risk, PrEP could be as cost-effective as earlier ART. Third, in couples that remain at high risk, PrEP and ART could be used sequentially (PrEP in the uninfected individual prior to ART initiation for their HIV-1-infected partner) to deliver maximal benefit and best cost-effectiveness.

A similar preliminary result was found in a mathematical model that examined the impact and cost-effectiveness of strategies, including earlier initiation of ART or PrEP, for HIV-1 prevention for serodiscordant couples in Nigeria. The results of the modelling suggest that the best first intervention strategy for discordant couples in Nigeria would be to ensure that all HIV positives are offered ART at current national guidelines. Additional reduction in new infections could be achieved by promoting condom use amongst discordant couples, offering PrEP to HIV negatives until their partner initiates ART or giving HIV positive partners TasP. Also, additional survival gains could be achieved through condom promotion for couples and TasP for HIV positive partners, which would also be incrementally cost-effective. However the impact was highly dependent on people taking the drugs consistently over long periods of time.

Several factors affect the cost effectiveness of PrEP vs. ART for prevention in serodiscordant couples (Figure 1). Once a method of PrEP is chosen, costing it out for the uninfected partner is straightforward: the same drug at the same interval for a given period. PrEP in the form of one tablet per day, for example, represents a predictable cost per year.

Costing out ART is more complicated. After infection with HIV, the CD4 count of an infected person declines from a normal value of about 1000 cells / microliter until, absent clinical intervention, a diagnosis of AIDS is warranted at a count of 200. Under current guidelines, ART should be initiated at a count of 500 cells / microliter or below. After ART begins, the CD4 count begins to rise again and the viral load drops until, after about six months, the viral load is undetectable. After viral suppression, the risk of HIV transmission to the uninfected partner is greatly reduced.

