The cost effectiveness question comes up if the infected person is the positive member of a serodiscordant couple. PrEP begins for the uninfected partner as soon as the infected partner is diagnosed and, since the uninfected partner is still uninfected, typically long before the CD4 count of the infected partner begins to decline. Once the infected partner presents an undetectable viral load, the risk of HIV transmission is greatly reduced. If this risk is less than or equal to the risk reduction provided by PrEP, then PrEP could be discontinued for the uninfected partner with no increase in risk. (The prevention strategy

---

after this point is called "Treatment as Prevention" or TasP.) PrEP is, therefore, a continuous cost from the moment of the diagnosis of the infected partner until six months after the infected partner starts ART. Under current guidelines that is six months after the infected partner's CD4 count falls to 350.

In the chart (Figure 1), the vertical dashed line is set at about 75%, which was the efficacy of the FTC / TDF method of PrEP found in the Partner's PrEP study. If viral suppression after ART in the infected partner protects the uninfected partner at least this effectively, then PrEP can be discontinued in favor of TasP and the differential costs saved.

This raises a question. Once started, ART becomes a continuous lifetime cost. If the infected partner is going to start ART at some point anyway, could the same risk reduction as PrEP have been bought for this couple at less total cost by starting ART at a CD4 count greater than 350? In other words, is it more cost effective to start ART earlier, thereby moving to TasP earlier, and save the expense of PrEP over the shortened period of high risk to the uninfected partner?

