The successful result of the HPTN 052 study and the recently released WHO ART guideline (which recommends commencing ART at a CD4 count of 500 instead of the previous recommendation of 350), which would promote access of HIV discordant couples to ART irrespective of CD4 count, also calls for careful guidance and planning especially for resource-constrained countries like Nigeria. Demonstration projects can enable a country to plan for cost effective roll out programs, thereby ensuring maximal benefit from invested resources.

HIV-1 serodiscordant couples are a primary target for implementation of ART for prevention (TasP) and PrEP. Critical unanswered questions for successful implementation of antiretroviral-based HIV-1 prevention include: how to target these expensive prevention strategies to realize maximum population HIV-1 prevention benefits; whether HIV-1 infected persons with asymptomatic disease would accept ART to reduce their risk for transmitting HIV-1; whether at-risk HIV-1 negative persons would use PrEP, and whether couples would sustain the high adherence needed for high effectiveness. Couples may potentially have the opportunity to use ART or PrEP for prevention; however, costs would prohibit simultaneous use in most settings. Thus, staged use – i.e., PrEP until the HIV-1 infected partner initiates ART and achieves viral suppression – may be an effective and cost-effective approach, and it is the approach we propose.

Successful implementation of ART and PrEP for prevention in HIV-1 serodiscordant couples will need to 1) target delivery to highest-risk couples, 2) respond to couples' preferences for and barriers to use of PrEP and ART, 3) achieve high uptake and sustained adherence and 4) consider how to discontinue PrEP if the HIV-1 infected partner initiates ART. This study proposes to address these key questions. In addition, for resource-poor settings like Nigeria, such PrEP demonstration projects must be able to show clearly models for effective target delivery of PrEP in a way that can ensure access and scale up of PrEP access by those who are at higher risk of contracting HIV infection beyond this initial target population thereby positively impact the National HIV epidemic.

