## 2.0 Study Method

This is a demonstration project to evaluate the effectiveness of three models for the delivery of PrEP and TasP as part of a combination prevention strategy for serodiscordant couples in three states in Nigeria. The overall goal is to identify the best model to facilitate uptake of PrEP as part of a comprehensive HIV prevention package for the HIV negative partner in serodiscordant relationships whose HIV positive partner has not begun ART or

---

has been on ART for less than six months. PrEP (daily oral FTC / TDF) will be offered to the HIV-1 uninfected partner. Uptake of PrEP and TasP and adherence to PrEP will be measured. Factors (individual, facility and community level) that facilitate PrEP and TasP uptake and adherence to PrEP will also be assessed.

HIV-1 infected participants will be offered the opportunity to use ART support services regardless of their CD4 count. This is in line with the current national guidelines on HIV treatment for adults and adolescents (2010:13). The current guidelines enable HIV positive individuals in discordant relationships to have access to ART irrespective of the CD4 count. This project will therefore serve as a measure of the effectiveness of this program in Nigeria.

For each couple, if the HIV-1 infected partner initiates ART, we will discontinue PrEP for the HIV-1 uninfected partner six months later (once viral suppression is typically achieved). If the HIV-1 infected partner declines to initiate ART, or initiates and discontinues, we will continue PrEP. Mixed-methods work will be conducted to understand user preferences, couples decision-making, and barriers to uptake of and adherence to both PrEP and ART.

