At enrollment HIV-1 uninfected women will have a pregnancy test to confirm eligibility (must not be pregnant to complete enrollment). Women will be asked about pregnancy at every scheduled follow-up visit and pregnancy testing will be done when clinically indicated (e.g., missed menses, participant request); PrEP will be continued during pregnancy and breastfeeding. In addition, pregnant women will be advised to continue with their follow up visits. When these participants no longer have a positive pregnancy test, the pregnancy outcome will be documented.

Every 6 months, in addition to regular quarterly visit procedures, CD4 counts and plasma viral loads will be done for HIV-1 infected partners.

Clinical safety will be assessed pre-, during- and post-enrollment. Laboratory safety assessments will be done at enrollment, month 12, study exit and additionally if indicated. At these visits, blood samples will be collected for urea, electrolytes, creatinine, liver function tests, full blood count, calcium and phosphate levels.

All HIV-1 infected partners who are interested in starting ART independent of their becoming eligible for ART under the current national guidelines, will be offered ART. Once the HIV-1 infected partner has been using ART for 6 months, PrEP will be discontinued for the HIV-1 uninfected partner, after counseling to the couple.

During follow-up, HIV-1 infected and uninfected participants will complete a quantitative interview to capture evolution in preferences to uptake of antiretroviral-based HIV-1 prevention and fertility intentions and any risk compensation behaviours. Questionnaires will be administered separately to both members of couples.

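### PrEP stops at six months of index ART with no exception for an index partner whose scheduled viral load is unsuppressed, although the protocol's rationale is to continue PrEP until suppression

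*Protocol*

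**What the plan says.** The operative rule appears twice. Section 2.0 says that if the index partner starts ART, "we will discontinue PrEP for the HIV-1 uninfected partner six months later (once viral suppression is typically achieved". Section 11.5 says: "Once the HIV-1 infected partner has been using ART for 6 months, PrEP will be discontinued for the HIV-1 uninfected partner", after the couple has been counselled. The exception in 2.0 is for an index partner who declines ART, or who starts and then discontinues it; PrEP then continues. The other stopping rules are a PrEP-related serious adverse event (11.12) and seroconversion (11.5). None refers to the index partner's viral load.

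The strategy is described differently elsewhere. The Summary has the index partner start ART "and sometime later achieves viral suppression. At this point as TasP strategy can be adopted and PrEP ended". Section 1.5 defines the proposed staged use as "PrEP until the HIV-1 infected partner initiates ART and achieves viral suppression". Section 1.4 bases stopping on the index partner having an undetectable viral load, then turns this into time: "the viral load drops until, after about six months, the viral load is undetectable", so that PrEP is a cost "until six months after the infected partner starts ART". Section 1.1 is more guarded, describing ART as "reducing HIV-1 plasma concentrations to undetectable levels within 6 months of initiation in the majority of persons".

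On the data, viral load is part of index screening (11.4) and is repeated in follow-up: "Every 6 months, in addition to regular quarterly visit procedures, CD4 counts and plasma viral loads will be done" (11.5). On entry, 4.0 recruits couples whose index partner is unsuppressed despite ART. Section 7.3 admits index partners on ART above 5000 copies/ml and sets no limit on ART duration; the goal in 2.0 refers to less than six months.

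**The concern.** The stop is justified by suppression but triggered by elapsed time, and the measurement that would tell the two apart is already scheduled. The proxy is claimed to hold for most people, not all, and the entry criteria deliberately admit some index partners who are viraemic on ART.

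What is at stake is the protection of the uninfected partner. Staff who follow 2.0 and 11.5 exactly would withdraw PrEP from the partner of an index patient known to be viraemic. Condoms, risk-reduction counselling and quarterly clinical monitoring (6.0), together with the counselling before the stop (11.5), reduce the risk, but none makes the stop depend on suppression. Nor does clinical judgement clearly fill the gap: 16.2 gives failure to discontinue product when protocol criteria require it as an example of a violation. Infections after the switch would also count towards the primary measure of 3.1.1, infections averted by PrEP and TasP.

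**Working it through.** The protocol gives no figure behind the six-month rule, so there is none to reproduce. The check is whether a usable viral load exists when the rule acts, and what it would cost to use it.

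**Inputs.** Stop after six months of ART (2.0, 11.5); viral load every six months (11.5); follow-up visits for up to 18 months (11.0). Assumption: draws fall at study months 6, 12 and 18.

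**ART started in the study at month s (0 to 12).**
- Planned stop = s + 6.
- Latest draw by the stop: d = 6 × floor((s + 6)/6).
- Time on ART at that draw = d − s.
- If that draw is unsuppressed and PrEP continues to the next one, at d + 6, extra PrEP = (d + 6) − (s + 6) = d − s.

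| s | Planned stop | Latest draw | ART months at draw | Extra PrEP if unsuppressed, then suppressed |
|---|---|---|---|---|
| 0 | 6 | 6 | 6 | 6 |
| 1 | 7 | 6 | 5 | 5 |
| 3 | 9 | 6 | 3 | 3 |
| 5 | 11 | 6 | 1 | 1 |
| 6 | 12 | 12 | 6 | 6 |
| 9 | 15 | 12 | 3 | 3 |
| 12 | 18 | 18 | 6 | no later draw within the visits |

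On this calendar every in-study start has an on-ART draw by the stop. Because d − s is both the ART duration at the draw and the length of the extension, an early and less informative draw (ART month 1) delays the stop by only 1 month. Each further unsuppressed draw adds 6 months.

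**Index partner admitted on ART with a = 1 to 5 months already taken.** If the clock starts at enrolment, the stop is month 6 and coincides with a draw, at 6 + a = 7 to 11 months of ART. If earlier ART counts, the stop is month 6 − a = 5 down to 1, with only the screening value, above 5000 copies/ml, on file.

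**A stricter alternative, for comparison.** Suppose every couple waited for a suppressed draw at or after six months of ART. The earliest stop would be 6 × ceil((s + 6)/6). Take one couple per start month 0 to 12, all suppressed, and count post-PrEP follow-up to month 18:
- Current plan: sum of (12 − s) = 12 + 11 + … + 0 = 78 couple-months.
- Stricter rule: 12 (s = 0) + 6 × 6 (s = 1 to 6) + 6 × 0 (s = 7 to 12) = 48 couple-months.
- Loss = 30/78 = 38%, with nothing left for starts at months 7 to 12.

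A rule that delays the stop only after an unsuppressed result leaves the 78 couple-months intact when all are suppressed, apart from result turnaround where draw and stop coincide (s = 0, 6, 12).

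**The case against.** The strongest reply is that the time rule is deliberate, consistent and disclosed. It is stated in 1.4, 2.0 and 11.5; the short-term PrEP modelled in 1.7 also ends by reference to the partner having started ART; and the project wants a delivery model that limits interference with real-world behaviour (6.0). A laboratory trigger for every couple would change the model being costed and would lose much of the post-PrEP follow-up, as the 78 to 48 comparison shows. That stands, and it is why the six-month default should remain. It does not explain why an unsuppressed result already on file should make no difference.

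Several stronger readings are tempting but unsupported:
- **That staff are told to disregard the viral load.** The protocol is silent; the point rests on the absence of an exception.
- **That PrEP stops at study months 1 to 5 for those admitted on ART.** This needs 11.5 to count ART taken before enrolment. Section 2.0, which counts from initiation, reads more naturally as ART started in the study.
- **That index partners above 5000 copies/ml at entry are failing treatment.** Section 2.0 describes under six months of ART, so some may simply be early.
- **That nothing covers an index partner who stops ART.** The continuation rule in 2.0 has no time limit and could be stretched to cover later stopping. It does not spell out resumption after withdrawal, or rebound on ART.
- **That post-switch infections bias the 3.1.1 measure.** They are outcomes of the strategy under evaluation, so counting them is correct.

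**Conclusion.** The point holds as a gap in a treatment-stopping rule, and it should be closed. Sections 2.0 and 11.5 can withdraw PrEP while the index partner has an unsuppressed scheduled result, contrary to the strategy in the Summary, 1.4 and 1.5. The matter belongs in the protocol, not in an analysis plan. The restart wording is a minor clarification.

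The size is limited to couples whose index partner stays on ART and is unsuppressed at the relevant draw. The protocol gives no such proportion, so neither affected couples nor infections can be counted. The timing results rest on draws at months 6, 12 and 18. Section 11.0 puts visits at month 1 and quarterly thereafter, which could also mean months 1, 4, 7, 10, 13 and 16. If the first draw then fell at month 7, an index partner starting ART at enrolment would reach the month-6 stop without an on-ART result.

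**What to change.** In 2.0 and 11.5:
1. Keep six months as the default stop, counted from ART start in the study or, for index partners admitted on ART, from enrolment.
2. Do not stop PrEP if the most recent scheduled on-ART viral load is above a threshold stated in the protocol; continue until a scheduled viral load shows suppression. State the draw months, and that a result pending at the stop date is awaited.
3. For index partners admitted on ART above 5000 copies/ml, require one suppressed scheduled follow-up viral load before the stop.
4. Add one sentence: PrEP is re-offered, after a negative HIV test, if the index partner later stops ART or a scheduled viral load shows rebound.

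Cost: wording, and a record of the result used. No draw is added or moved. On the assumed calendar, PrEP lasts 1 to 6 months longer after one unsuppressed result if the next draw is suppressed, and 6 months more for each further unsuppressed draw. An unsuppressed draw at month 18 has no later draw within the visits. These couples lose some or all of their post-PrEP follow-up, and the economic costs under 3.1.2 rise slightly, since they count the full value of resources even for donated drug. In Plateau, refills move to satellites while six-monthly laboratory work stays at the central hospital (2.0), so results must be passed on before refills end. Couples with a suppressed result stop as planned, apart from any wait for a pending result.

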### 3.0 Objectives

#### 3.1 Primary objectives

- 3.1.1 Optimize, implement and evaluate the effectiveness of an implementation model which integrates PrEP and TasP provision into existing service provision centres.
- 3.1.2 Estimate the cost and cost effectiveness of the PrEP and TasP demonstration project.
- 3.1.3 Model the resources needed to provide scaled up PrEP and TasP access for serodiscordant couples in Nigeria.

**Objective 3.1.1: To optimize, implement and evaluate the effectiveness of an implementation model which integrates PrEP and TasP provision into existing service provision centres.**

The demonstration project will be evaluating the effectiveness of a model of HIV service delivery to couples that promotes and ensures effective PrEP access. Such a model should be able to ensure effective community engagement in ways that improve and support a couple's access and uptake of HIV prevention and treatment interventions, ensure access in hard to reach areas where there are few health facilities, and support sustained quality and consistency of PrEP and TasP services irrespective of place of delivery. The model for delivery of ART based HIV intervention programs for couples for this demonstration project would be designed based on feedback received during the formative research conducted to support this research. The study outcome should help critical stakeholders know how well the study model was able to achieve the desired PrEP service delivery into family planning services. This will help inform decision making on how to institutionalize the program, strategies that are economical and efficient, and how best to make modifications to the program implementation model to increase effectiveness.

The primary outcome of this objective is the measure of the impact that project intervention had on serodiscordant couples' access, uptake and retention in the antiretroviral-based HIV-1 prevention program. Formative and summative evaluations would be conducted. Formative evaluation will be conducted at months 6, 12 and 18 with derived information use to modify the program so as to increase its efficiency. The summative evaluation will be conducted at the end of the project and would help to decide on the effectiveness of the program.

*The primary measure of this objective will be the number of new infections averted by the use of PrEP and TasP.*

